### Study setting and location

This study is currently being conducted at a level 3 NICU at the Women’s Hospital School of Medicine Zhejiang University in China, where more than 300 LBW infants are being treated per year. A total of 105 beds are available in the NICU wards, with more than 100 pediatricians and nurses.

### Study population

All the infants will be delivered either vaginally or by C-section in the hospital. Infants with GA ≥ 31 weeks and/or with BW 1500–2300 g will be transferred to the NICU. Male and female healthy preterm infants will be selected from the NICU according to the inclusion criteria.

### Patient adherence

To ensure participant adherence, the investigator will maintain close contact with the fathers in the SSC group and coordinate the intervention time with fathers at their convenience. Fathers may withdraw from the trial for any reason at any time. Fathers who commit to participation but miss several sessions of SSC because of work or time limitations will be allowed.

### Inclusion criteria:

GA between 32^0^ and 34^6^ weeks with BW ≥ 1500 gApgar scores at 1 min and 5 min ≥ 7Vaginal or caesarean deliveryMedically stable for 24–72 h (definition of stability is based on the infant’s vital signs, with temperature ranging from 36.5 to 37.5 °C, SpO_2_ > 90%, respiratory rate < 60/min, heart rate of 100 beats/min to 180 beats/min)

### Exclusion criteria:

Congenital anomaliesMetabolic diseasesSevere periventricular/intraventricular hemorrhage (IVH, Grades III–IV)History of minor or major surgeryHospitalization duration of less than 2 weeksInfants belonging to single-parent familiesInfants with intubation and mechanical ventilation

### Trial treatments

All infants admitted to the NICU will be given parenteral nutrition, cared for under radiant warmers, and treated with further interventions according to the health status of the infants. After the initial stabilization, infants will be randomly assigned to either the SSC group or the TC group according to randomization and allocation rules.

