**Fig. 1 Fig1:**
[figure not shown]
Flowchart of study design

**Table 1 Tab1:** Schedule of enrollment, interventions, and assessments

Time point	Study Period								
	Enrolment	Allocation	Post-allocation						
	*-t* _*1*_		*t* _*1*_	*t* _*2*_	*t* _*3*_	*t* _*4*_	*t* _*5*_	*t* _*6*_	*t* _*7*_
Enrolment:									
Eligibility screen	X								
Informed consent	X								
Randomization and allocation		X							
Interventions:									
SSC group			X						
TC group			X						
Assessments:									
State-Trait Anxiety Inventory, STAI				X		X			
Salivary cortisol					X				
Brazelton Neonatal Assessment Scale, BNAS						X			
Neuroimaging							X		
Infant Neurological International Battery, INFANIB							X		
Paternal Postnatal Attachment Scale, PPAS								X	X

t_1_ = During hospitalization

t_2_ = 1 day to 3 days after birth

t_3_ = 10-15 days after birth

t_4_ = 37 weeks of corrected age or before discharge

t_5_ = 38-42 weeks of corrected age

t_6_ = 4 months after discharge

t_7_ = 6 months after discharge

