### Intervention group

Infants in the intervention group will be offered SSC as soon as they are stable (approved by a pediatrician in the unit), and they are expected to receive SSC every day during hospitalization. SSC will be performed between 4:00 pm and 6:00 pm for at least 1 h in a private room adjacent to the unit with an ambient temperature between 22 and 24 °C and appropriate light and sound levels. Fathers will wear a comfortable gown and be seated on a reclining chair at an angle of 40 to 60°. Each infant will be taken out of the incubator, unclothed (only diaper and cap are kept on), and placed in an upright position on the father’s chest. The infants will be covered by a blanket to keep them warm. Fathers will be educated on how to hold the infant correctly and encouraged to watch their child and talk to them. Father and baby will be left in the kangaroo position for at least 1 h. During SSC, infants will remain attached to a cardiorespiratory monitor and will be observed by a nurse; routine nursing including parenteral nutrition administration and IV injection can also be performed. Because SSC is not routine care in our hospital, this practice will follow the World Health Orgainization (WHO) guidelines [63].

If hypothermia or apnea of any duration accompanied by desaturation occurs during the SSC, the intervention will be discontinued, and the eligibility of the infant will be reassessed. Infants in the intervention group will receive the same standard treatment as infants in the TC group except for at least 1 h of SSC every day.

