## Outcome measures

### Primary outcome measure

The primary outcome is the neurodevelopmental outcomes of preterm infants, which will be measured by salivary cortisol and PIPP during hospitalization (at the age of 10–15 days) and by INFANIB and neuroimaging at term-equivalent age (40 weeks of corrected age).

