### Assignment of interventions

#### Allocation

A simple random sampling method is used. Fifty numbers are generated from a list of randomization codes by a medical staff member who is not involved in the experiment. The numbers are ordered from small to large; the first 25 numbers are set to be the intervention group, and the remaining numbers are set to be the control group. Fifty numbers are mixed and then put into opaque, sealed envelopes. When a preterm infant meets the inclusion criteria, he or she is assigned to either the intervention group or the control group according to the randomly generated number by a medical staff member who is not involved in the experiment.

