### Data analysis

The data analysis will be conducted on an intention-to-treat basis. All the study subjects will be analyzed in the groups into which they were originally randomized.

Descriptive characteristics will be analyzed using frequencies and percentages. The independent *t* test and a repeated measures analysis of covariance (RM-ANCOVA) will be used to compare differences between the two groups for continuous variables. Categorical variables will be compared using the Pearson chi-square test or Fisher’s exact test. *P* values less than 0.05 will be considered significant. Data will be analyzed using the statistical software SPSS 23.0 (IBM SPSS Statistics, IBM Corporation, Armonk, NY, USA).

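### Excluding infants with a hospital stay under two weeks cannot be checked at randomisation and, applied as written, conflicts with the intention-to-treat rule

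*Protocol article*

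**What the plan says.** All references are to the Protocol article.

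- **Exclusion criteria:** infants whose hospital stay is shorter than two weeks are excluded. Nothing there or elsewhere says that an expected or anticipated stay is meant.
- **Inclusion criteria:** the infant must have been medically stable for 24–72 h.
- **Trial treatments:** "After the initial stabilization, infants will be randomly assigned to either the SSC group or the TC group".
- **Allocation:** "When a preterm infant meets the inclusion criteria, he or she is assigned to either the intervention group or the control group". Fifty numbers are placed in sealed envelopes, 25 for each arm.
- **Intervention group:** "Infants in the intervention group will be offered SSC as soon as they are stable", and SSC then continues daily through the hospital stay.
- **Primary outcome measure and Table 1:** salivary cortisol and the Premature Infant Pain Profile (PIPP) are measured "at the age of 10–15 days". Table 1 gives the cortisol time point as "10-15 days after birth".
- **Data analysis:** "The data analysis will be conducted on an intention-to-treat basis", and "All the study subjects will be analyzed in the groups into which they were originally randomized".

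**The concern.** An exclusion criterion has to be decidable when the envelope is opened. This one is not. On the day of allocation nobody knows how long the infant will stay, and by the time the answer is known the SSC arm has been treated.

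That leaves two readings. Either the criterion cannot be used at screening, or it is used after randomisation. In the second case it takes randomised infants out of the trial, and the promise to analyse everyone as randomised cannot be kept.

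Removal might also differ between the arms. Care is visibly different (a daily session with the father in a separate room, against incubator or radiant-warmer care), so staff who judge readiness for discharge can know the allocation. The Background also cites less infection and severe illness with kangaroo care, so an effect on length of stay is conceivable. If more early-recovering infants were removed from the SSC arm, those left there would be a somewhat sicker group.

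The two-week cut also falls inside the measurement window for cortisol and PIPP. An infant discharged on day 11 to 13 could have complete data on both and still meet the exclusion.

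**Working it through.** **1. Timing.** If an infant is stable from birth and the stay is counted from birth, allocation falls on about day 1 to 3. The criterion is settled at discharge or at day 14, whichever comes first. At the latest that is 14 − 3 = 11 to 14 − 1 = 13 days after allocation. Later stabilisation shortens the gap, but the status is still open when the infant is allocated.

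**2. The stated sample size.** Inputs from Sample size: means 0.21 and 0.57, SDs 0.12 and 0.61, two-sided type I error 5%, type II error 20%.

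- Difference = 0.57 − 0.21 = 0.36
- SD = √((0.12² + 0.61²)/2) = 0.4396
- d = 0.36/0.4396 = 0.819
- n per arm from the noncentral t distribution = 24.41, rounded up to 25
- Power at 25 per arm = 0.810

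The stated 25 per arm reproduces. It leaves almost no slack above 80%.

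**3. Power if infants are removed.** The documents give no share of stays under two weeks, so the share is an assumed range, equal in both arms, with d = 0.819.

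| Removed from each arm | n per arm | Power |
|---|---|---|
| 0% | 25 | 0.81 |
| 5% | 23.75 | 0.79 |
| 10% | 22.5 | 0.77 |
| 20% | 20 | 0.71 |
| 30% | 17.5 | 0.65 |

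**4. Bias if removal differs by arm.** This step assumes:

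- normally distributed stays;
- a correlation of 0.5 between stay and outcome;
- SSC shortening the stay by 2 days, with no other effect on the outcome.

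The removed share p in an arm is the probability of a stay under 14 days. The mean severity of those who remain, in SD units, is φ(z)/(1 − p) with z = Φ⁻¹(p). The bias is 0.5 times the difference between arms.

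| Assumed mean/SD of stay (control arm) | Removed, control | Removed, SSC | Power | Severity difference | Bias |
|---|---|---|---|---|---|
| 18/5 days | 21% | 34% | 0.66 | 0.19 SD | 0.10 SD |
| 22/7 days | 13% | 20% | 0.73 | 0.11 SD | 0.05 SD |
| 25/7 days | 5.8% | 9.9% | 0.78 | 0.07 SD | 0.04 SD |
| 25/5 days | 1.4% | 3.6% | 0.80 | 0.05 SD | 0.02 SD |

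The 25-day rows are a rough anchor. Table 1 places the discharge assessment at 37 weeks or before discharge. From 32 weeks 0 days, 37 weeks 0 days is 35 days away; from 34 weeks 6 days it is 15. The midpoint is (35 + 15)/2 = 25 days. This is not a stated length of stay, and discharge may come earlier.

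If SSC does not change the stay, the bias is zero in every row. Power is then 0.71 (18/5), 0.75 (22/7), 0.78 (25/7, rounded down from 0.785) and 0.80 (25/5).

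**The case against.** The strongest reply is that the authors meant an expected stay, judged at screening, and that a condensed article simply left the word out. Table 1 puts the eligibility screen before randomisation, and Data analysis keeps every subject in the randomised group. Read together, these suggest a screening criterion with nobody removed afterwards.

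Part of this stands. A reader might infer that the trial has announced it will drop randomised infants. It has not: no sentence says so, and the conflict with intention-to-treat arises only if the criterion is applied to the actual stay. A reader might also infer that removed infants could not be replaced because there are exactly 50 envelopes. The article is silent on replacement, so that does not follow.

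The reply does not cure the problem. The position of the eligibility screen in Table 1 cannot make an actual length of stay knowable on that day, and no text says that an expected stay is meant. Nor is eligibility plainly closed at allocation: the Intervention group section has it reassessed after certain events during SSC, which can happen in one arm only.

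On size, the objection is largely right. Stay distributions, a two-day shortening and the correlation are all assumptions. No passage says that about an hour of SSC a day shortens the stay of already stable infants. With a mean stay near 25 days the loss of power is slight.

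**Conclusion.** The criterion is wrong as written. It rests on a quantity unknown at allocation, and applying it literally removes randomised infants on a post-allocation event, against the analysis rule in the same article. This conclusion rests on the text alone and needs no assumption about length of stay.

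The size of the harm cannot be fixed from the documents. For the outcome used in the sample size calculation, power would fall from 0.81 to between 0.79 and 0.65 if 5% to 30% of each arm were removed. It would hardly change if short stays are rare. Bias is zero if removal is equal in both arms, and up to about 0.10 SD under the unequal removal tabulated above, beside a planning effect of 0.82 SD.

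Two stronger readings are not supported. One is that the arms become non-comparable on every outcome: that needs removal that differs by arm and is related to each outcome. The other is that power will be 66–73%: that depends on mean stays of 18 to 22 days and an SSC effect on stay, none of which the documents give.

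**What to change.** Do one of the following:

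- delete the length-of-stay criterion; or
- replace it with an expected stay of at least two weeks, as judged and recorded before the envelope is opened.

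In either case, state that all eligibility criteria are applied once, before allocation, and that every randomised infant stays in the analysis whatever the actual stay. The sentence on reassessing eligibility during SSC should be reconciled with this, so that it does not decide who is analysed. Whether SSC continues after such an event is a clinical matter outside this point.

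The heel stick should not be timed differently for infants who seem likely to leave early. That would tie measurement timing to a judgement made after randomisation, which could itself differ by arm.

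The cost is a short amendment, with no new data collection. Trial status describes recruitment as ongoing, so the change can be made before analysis. A small downside remains: infants discharged before day 10 will lack cortisol and PIPP, so power for cortisol may not return fully to 0.81. They can still contribute the term-age neurological assessment and imaging, the safety data and the fathers' scales.

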### Intervention group

Infants in the intervention group will be offered SSC as soon as they are stable (approved by a pediatrician in the unit), and they are expected to receive SSC every day during hospitalization. SSC will be performed between 4:00 pm and 6:00 pm for at least 1 h in a private room adjacent to the unit with an ambient temperature between 22 and 24 °C and appropriate light and sound levels. Fathers will wear a comfortable gown and be seated on a reclining chair at an angle of 40 to 60°. Each infant will be taken out of the incubator, unclothed (only diaper and cap are kept on), and placed in an upright position on the father’s chest. The infants will be covered by a blanket to keep them warm. Fathers will be educated on how to hold the infant correctly and encouraged to watch their child and talk to them. Father and baby will be left in the kangaroo position for at least 1 h. During SSC, infants will remain attached to a cardiorespiratory monitor and will be observed by a nurse; routine nursing including parenteral nutrition administration and IV injection can also be performed. Because SSC is not routine care in our hospital, this practice will follow the World Health Orgainization (WHO) guidelines [63].

If hypothermia or apnea of any duration accompanied by desaturation occurs during the SSC, the intervention will be discontinued, and the eligibility of the infant will be reassessed. Infants in the intervention group will receive the same standard treatment as infants in the TC group except for at least 1 h of SSC every day.

### Control group

Conversely, infants in the TC group will be cared for under radiant warmers or in the incubators and treated with routine nursing procedures. These infants will not receive any paternal SSC during hospitalization.

## Outcome measures

### Primary outcome measure

The primary outcome is the neurodevelopmental outcomes of preterm infants, which will be measured by salivary cortisol and PIPP during hospitalization (at the age of 10–15 days) and by INFANIB and neuroimaging at term-equivalent age (40 weeks of corrected age).

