**Methods/design:**

A randomized controlled trial will be used to investigate the effects of paternal-infant SSC in NICU wards in China. Preterm infants born at a gestational age in the range of 32^0^–34^6^ weeks with a birth weight > 1500 g will be eligible. A simple random sampling method will be used to allocate infants to the SSC group (*n* = 25) or the TC group (*n* = 25). After medical stability, infants in the SSC group will be provided SSC by fathers for one hour every day until discharged from hospital. The primary outcome is neurodevelopmental measures, specifically salivary cortisol and Premature Infant Pain Profile (PIPP) during hospitalization. At 40 weeks of corrected age, infants will be assessed using the Infant Neurological International Battery (INFANIB) and neuroimaging. Secondary outcomes include infants’ physiological stability during SSC and throughout hospitalization and state observation at discharge. The fathers’ mental health will be assessed with the State-Trait Anxiety Inventory (STAI) 1 day to 3 days after the infant’s admission to the NICU and at discharge. Father-infant attachment will be evaluated at 4 and 6 months after the infants’ discharge, measured by the Paternal Postnatal Attachment Scale (PPAS). Statistical analyses will be conducted using a two-sided significance level of 0.05.

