## Objectives

### Primary objective

The primary objective of this trial is to study the effect of early paternal SSC versus traditional care (TC) on neurodevelopmental outcomes measured by salivary cortisol, the PIPP, the Infant Neurological International Battery (INFANIB), and neuroimaging.

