#### Magnetic Resonance Imaging (MRI)

Quantitative MRI will be used to observe preterm infants’ brain growth at term-equivalent age. Total cerebral volume, volumes of white and gray matter, and the cerebral cortex will be measured to predict brain development in preterm infants.

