### Sample size

The sample size is calculated based on the results from Xiaomei Cong [19] on the level of salivary cortisol of study 2, KCH (kangaroo care heel stick study condition): mean (M) = 0.21, standard deviation (SD) = 0.12; IH (incubator heel stick study condition): M = 0.57, SD = 0.61. We estimate that a sample size of 25 participants per group (50 in total) would be sufficient to detect a difference between the experimental group and the control group, assuming a two-tailed test for a type I error of 5% and a type II error of 20%. This sample size is calculated using the G*Power 3.1.9.2 software. Additional file 1 details the sample size calculation.

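### Four unranked primary measures are judged at P < 0.05 with no success rule, while the sample size rests on salivary cortisol alone

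*Protocol article*

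**What the plan says.** - **Primary objective:** the effect of paternal skin-to-skin contact on "neurodevelopmental outcomes measured by salivary cortisol, the PIPP, the Infant Neurological International Battery (INFANIB), and neuroimaging".
- **Primary outcome measure:** neurodevelopment, "which will be measured by salivary cortisol and PIPP during hospitalization (at the age of 10–15 days) and by INFANIB and neuroimaging" at 40 weeks of corrected age. Neither section orders the four measures, combines them, or says how many must be significant.
- **Magnetic Resonance Imaging (MRI):** the imaging measure is itself a set: "Total cerebral volume, volumes of white and gray matter, and the cerebral cortex will be measured".
- **Abstract, Methods/design:** "Statistical analyses will be conducted using a two-sided significance level of 0.05".
- **Data analysis:** P "values less than 0.05 will be considered significant", with no distinction between primary and secondary comparisons.
- **Sample size:** the calculation is based "on the level of salivary cortisol of study 2" of a cited trial (kangaroo care mean 0.21, SD 0.12; incubator mean 0.57, SD 0.61). It assumes a two-tailed 5% type I error and a 20% type II error, and arrives at 25 per group.

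**The concern.** A type I error of 5% and a power of 80% are properties of a decision rule. The protocol states both figures but does not give the rule for its primary objective. Two readings are open, and the stated figures fit neither:

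- **Any one of the four is enough.** Each test spends the full 5%, so the error for the primary objective as a whole exceeds 5%.
- **All four are needed.** The error is controlled, but power is the chance that all four succeed together, and only one of them was sized.

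The Discussion says the data may be used to promote early paternal contact in the NICU and to modify guidelines. With the rule left open, the choice of which result answers the primary question could be made after the results are seen.

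**Working it through.** **1. Reproduce the stated sample size.** Inputs from the Sample size section: means 0.21 and 0.57, SDs 0.12 and 0.61, two-sided alpha 0.05, power 80%, equal groups.

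- Pooled SD = √((0.12² + 0.61²)/2) = 0.4396
- d = (0.57 − 0.21)/0.4396 = 0.36/0.4396 = 0.819
- Two-sample t test (noncentral t): 24 per group gives 79.3% power, 25 per group gives 81.0%

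The stated 25 per group reproduces. It is right for one cortisol comparison at an undivided 0.05.

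**2. Any one measure suffices.** The chance of at least one P < 0.05 among k independent tests when no measure has a true effect is 1 − 0.95^k.

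- k = 4: 1 − 0.8145 = 18.5%
- k = 7 (cortisol, PIPP, INFANIB and four volumes, if each volume is tested): 1 − 0.6983 = 30.2%

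The protocol gives no correlations between the measures, so these are assumptions. Simulating equally correlated normal test statistics (500,000 draws) gives:

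| Common correlation | 4 tests | 7 tests |
|---|---|---|
| 0.3 | 17.3% | 27.1% |
| 0.5 | 15.5% | 23.0% |
| 0.7 | 13.0% | 17.8% |
| 0.8 | 11.4% | 14.9% |
| 0.9 | 9.3% | 11.4% |

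The volumes overlap anatomically, so the independent seven-test figure is an upper value. If the four volumes correlate at 0.8 and the other three measures are independent of them and of each other, the chance is 1 − 0.95³ × (1 − 0.114) = 1 − 0.8574 × 0.886 = about 24%.

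**3. All four must be significant.** The error stays at or below 5%. Joint power cannot exceed that of the cortisol test alone, 81.0%. As an illustration only, if the other three measures each had 81% power and all four were independent, joint power would be 0.81⁴ = 43%. The protocol gives no effect sizes for PIPP, INFANIB or MRI, so the true figure cannot be computed.

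**4. What dividing alpha would cost.** Same d of 0.819, Bonferroni split:

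| Primary tests | Alpha per test | Cortisol power at 25 per group | Per group for 80% |
|---|---|---|---|
| 1 | 0.05 | 81.0% | 25 |
| 4 | 0.0125 | 61.9% | 35 |
| 7 | 0.00714 | 53.8% | 40 |

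Under Holm across four tests, cortisol faces 0.0125 only when no other measure has yet been rejected. The 61.9% is therefore the lower limit of its power.

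**The case against.** **Multiplicity belongs in the analysis plan.** A journal article often leaves the adjustment to a separate plan, which is not shown here. That is fair, and the mere absence of an adjustment is not the point. What the article itself fixes is an unranked set of four primary measures, a flat 0.05 threshold and a sample size for one of the four, and these do not fit together.

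**No one-is-enough rule is stated.** This stands. A reader might infer that the plan lets any single significant result count as success, but no section says so. The inflation is therefore conditional on that rule.

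**The seven-test count is inferred.** This also stands. The MRI section says the volumes will be measured, not that each is a separate primary test. Four is the number to lead with.

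**Three stronger readings go too far.**

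- A reader might conclude that a positive trial has more than a 5% chance of being false. The figures above are the chance of at least one significant primary result when nothing works, which is a different quantity.
- A reader might see a contradiction in the Abstract, which says "The primary outcome is neurodevelopmental measures, specifically salivary cortisol and Premature Infant Pain Profile (PIPP) during hospitalization". The next sentence adds INFANIB and neuroimaging, ahead of the secondary outcomes, so in sequence it can be read as listing the same four. The wording is awkward and worth aligning, but it is weak evidence of conflict.
- A reader might object that cortisol and PIPP are not neurodevelopmental measures. That is a dispute about constructs, on which the Background gives a rationale linking pain exposure to later outcomes. It is separate from the error rate.

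**Conclusion.** The point holds in conditional form, and it should be settled before analysis. As written, the 5% error and the 80% power describe one cortisol comparison, not the primary objective.

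- If any one measure suffices, the error for the primary objective is 18.5% under independence. It stays at about 9% or more over the assumed correlations up to 0.9. Separate testing of four MRI volumes would raise it, to at most about 30%.
- If all four are required, there is no inflation, but power for that rule is not calculated and cannot exceed the 81% for cortisol.

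The sample-size arithmetic is correct for cortisol. The results rest on the cited trial's means and SDs as quoted in the protocol, on normal test statistics, and on correlations assumed because none are given.

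**What to change.** **Preferred.** In the Abstract, Primary objective and Primary outcome measure sections, name one primary measure, time point and sample. Salivary cortisol at 10–15 days is the only candidate the sample size supports, and 25 per group (81% power) then stands. The text should say which sample or contrast is meant, because two are collected, before and after the heel stick, and the Sample size section says only that the level is used. Make PIPP, INFANIB and each MRI volume secondary, either with Holm-adjusted P values or with estimates and 95% confidence intervals labelled supportive.

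**Alternative.** If the investigators prefer to keep all four as primary because their question is neurodevelopment, state a multiplicity procedure such as Holm, and say whether the MRI volumes enter as one test or several. Then restate the cortisol power: about 62% at 0.0125 with 25 per group, or 35 per group (70 in total) to restore 80%.

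**Cost.** The preferred change needs wording and no extra infants, but PIPP, INFANIB and MRI then no longer carry a primary claim. The first participant was recruited in September 2017, so either route is a mid-trial amendment. It should be dated, made before any unblinded look at the data, and entered in the registry.
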